### Study Investigations

The F-FIT will conduct a range of assessments at baseline, 4-months, and 12-months. The study design is outlined in Figure 7, and the assessments are summarized in Table 2. In brief, all participants will undergo a detailed evaluation of aerobic exercise capacity, respiratory muscle and lung function, body composition, musculoskeletal fitness, endothelial function, quality of life, neurocognitive and neuropsychological function, neurohormonal activation, liver stiffness, dietary intake and nutritional status, metabolites, habitual physical activity levels, and cardiac function. Follow-up visits will be conducted within 15 days of the scheduled reassessment date. If a testing date cannot be scheduled within 15 days, participants in the intervention groups may continue exercise training in accordance with the protocol to prevent detraining for up to 31 days.

**Figure 7 F7:**
[figure not shown]
The Fontan Fitness Intervention Trial (F-FIT) study design flow diagram.

**Table 2 T2:** Assessments and testing.

	**Outcomes measures**	
Cardiopulmonary exercise testing	Aerobic exercise capacity (peak VO_2_)^‡^, V_E_/VCO_2_ ratio and slope, RER, HR, OUES, VO_2_ at AT, work rate, oxygen pulse, VO_2_/work rate slope, and peripheral venous pressure	
Respiratory muscle and lung function tests	FEV_1_, FVC, FEV_1_/FVC ratio, TLC, DL_CO_, PImax, and PEmax	
Dual-energy x-ray absorptiometry	Lean mass, fat mass, bone mineral content, and bone mineral density^†^	
Liver elastography	Liver stiffness	
Near-infrared spectroscopy^†^	HHb, HbO_2_, and skeletal muscle oxidative capacity	
Neurocognitive function assessment (Cogstate)	Psychomotor function, attention, visual learning and memory, verbal learning and memory, processing speed, social-emotional cognition, working memory, and executive function scores	
Habitual physical activity (accelerometers; Actigraph GT9X Link)	Counts per minute, steps per day; and time spent in sedentary, light, moderate, vigorous, and moderate-to-vigorous activity	
Nutrition and dietary assessments (ASA24, SGA^†^ or SGNA^†^, GSRS^†^, and indirect calorimetry^†^)	SGA (in adults)/SGNA (in children) classification of nutritional status; GSRS (reflux, abdominal pain, indigestion, diarrhea, constipation scores, and total score); dietary macronutrient and micronutrient intake and composition, and REE	
Flow-mediated dilation (FMD)^†^	FMD% (Δ diameter), baseline diameter, peak diameter, and time to peak	
Laboratory and biochemical investigations	NT-proBNP and metabolomic analysis	
Transthoracic echocardiography	AVV S/D ratio, valvular function, VTI, annulus size, aortic flow, and ventricular function	
Resting and exercise cardiac MRI^†^	Ventricular volumes (end-diastolic, end-systolic, stroke volume), ejection fraction, flows (aortic, vena caval), diastolic function (feature tracking, T1 mapping E'), pulmonary artery size (Nakata index), lung water density, hepatic T1 mapping, and AV valve function	
Anthropometry and BIA	Height, weight, waist circumference, BMR, total body water, %BF, and skeletal muscle index	
Quality of life (PedsQL core and cardiac modules)	Physical functioning, emotional functioning, social functioning, school/work functioning, psychosocial functioning, heart problems and treatment, perceived physical appearance, treatment anxiety, cognitive problems, communication and total scores	
	**Adolescents and adults**	**Children**
Musculoskeletal fitness testing	Chest press 1RM, leg press 1RM, number of leg press repetitions at 70% 1RM (muscular endurance), and handgrip strength	Number of sit-ups, number of push-ups, standing long jump distance, and handgrip strength
Health economic analysis (EQ-5D-5L, CHU-9D, patient cost, and health care expenditure data linkage)	Health state in EQ-5D dimensions, patient cost, and health care utilization	CHU-9D scores, patient cost, and health care utilization

‡ *Primary outcome*,

† *Conducted in a subset of participants at selected sites. 1RM, one-repetition maximum; AT, anaerobic threshold; AV, atrioventricular; ASA24, automated self-administered dietary assessment tool; AVV S/D, atrioventricular systolic to diastolic duration; BIA, bioelectrical impedance analysis; BMR, basal metabolic rate; BF, body fat; DL_CO_, diffusing capacity of the lung for carbon monoxide; FEV_1_, forced expiratory volume in one second; FMD, flow-mediated dilation; FVC, forced vital capacity; GSRC, gastrointestinal symptom rating scale; HbO_2_, oxyhemoglobin; HHb, deoxyhemoglobin; HR, heart rate; MRI, magnetic resonance imaging; NT-proBNP, N-terminal pro b-type natriuretic peptide; OUES, oxygen uptake efficiency slope; PEmax, maximum static expiratory pressure; PImax, maximum static inspiratory pressure; REE, resting energy expenditure; RER, respiratory exchange ratio; SGA, subjective global assessment; SGNA, subjective global nutritional assessment; TLC, total lung capacity; VTI, velocity time integral; VE/VCO2, ventilatory equivalent for CO2; VO_2_, oxygen uptake*.

### Statistical Considerations

#### Power Analysis

Sample size calculations have accounted for a 10% dropout over 4-months.

##### Adolescents and Adults

This study will involve testing two hypotheses: the first involves demonstrating the superiority of the traditional exercise training group compared to the usual care group with regards to improvements in peak VO_2_. The second involves demonstrating that telehealth exercise training is non-inferior to traditional exercise training. Using this rationale, we based the sample size calculation for a three-arm trial with a randomization allocation of 2:2:1 using the R package Three *Armed Trials* (version 1.0-3).

We will require 110 adolescent and adult Fontan participants (44 each in the traditional and telehealth training groups and 22 in the usual care group) to achieve at least 80% power (two-sided α of 5%) to detect a difference of 10% in peak VO_2_ (standard deviation of 5%) between the traditional exercise training group compared to the control group. If there is a statistically significant difference between the traditional and control group (i.e., *p*-value < 0.05), then the test of non-inferiority will have 80% power (one-sided α of 2.5%) of showing that telehealth training retains at least 85% of the effect seen in traditional testing compared to control.

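### The stated 80% power for the telehealth non-inferiority test does not follow from the plan's own inputs; they give about 32%, or about 30% after the planned dropout

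*Protocol article*

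**What the plan says.** Under Power Analysis, Adolescents and Adults, the protocol article bases the calculation on a "three-arm trial with a randomization allocation of 2:2:1", with "44 each in the traditional and telehealth training groups and 22 in the usual care group", 110 in total. The first test compares traditional training with usual care. Its sample size is set "to achieve at least 80% power (two-sided α of 5"%), "to detect a difference of 10% in peak VO_2_ (standard deviation of 5"%).

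If that test is significant, the second follows: "the test of non-inferiority will have 80% power (one-sided α of 2.5%) of showing that telehealth training retains at least 85% of the effect" of traditional training over control. No separate effect, standard deviation or true telehealth effect is given for this second test. An R package for three-arm trials is named, without its inputs.

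The opening line of Power Analysis adds: "Sample size calculations have accounted for a 10% dropout over 4-months". The 110 is therefore the number randomized, and about 40/40/20 are expected to be evaluable.

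**The concern.** An 85% retention requirement is strict. On a 10-point effect it allows telehealth to lose only 1.5 points, which is 0.3 of a standard deviation. Ruling out so small a loss with 44 per training arm looks implausible, whereas the superiority test at two standard deviations is very easy to pass. One sample size is said to serve both tests, and the two demands are far apart.

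The test carries primary objective (c), whether telehealth is non-inferior to traditional training. If its real power is near 30%, the trial will most likely end without a positive answer on telehealth even when telehealth works equally well. Readers who were told the power was 80% could take that result as evidence against telehealth.

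**Working it through.** **Inputs** (all from Power Analysis, except the last)

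- Arms: traditional (R) 44, telehealth (T) 44, usual care (C) 22. After 10% dropout, about 40/40/20.
- R − C = 10 percentage points; SD = 5.
- Retention fraction 0.85; one-sided α = 2.5%, so the critical value is 1.960.
- Assumption, not stated in the article: the true telehealth effect equals the traditional effect (T = R). The range is shown below.

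**Superiority test (the plan's first figure)**

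SE = 5 × √(1/44 + 1/22) = 1.306, and 10/1.306 = 7.66. Power exceeds 99.99%, which is consistent with the stated minimum of 80%. The gate before the non-inferiority test is therefore passed almost surely.

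**Non-inferiority test (the plan's second figure)**

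Retaining at least 85% of the effect means T − C ≥ 0.85 × (R − C). The tested contrast is T − 0.85R − 0.15C > 0.

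- Expected value with T = R: 0.15 × 10 = 1.5 points.
- SE at 44/44/22: 5 × √(1/44 + 0.7225/44 + 0.0225/22) = 1.002.
- Power: Φ(1.5/1.002 − 1.960) = Φ(−0.463) = 32.2% (noncentral t: 31.7%).
- SE at 40/40/20: 5 × √(1/40 + 0.7225/40 + 0.0225/20) = 1.051.
- Power: Φ(1.5/1.051 − 1.960) = Φ(−0.533) = 29.7% (noncentral t: 29.2%).

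Simulation conditional on a significant superiority test gives 31.5% and 29.2%. The stated 80% is not reproduced.

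**Other readings**

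| Reading | 44/44/22 | 40/40/20 |
|---|---|---|
| Fixed 1.5-point margin, T versus R only | 29% | 27% |
| One-sided α of 5% | 44% | 41% |
| One-sided α of 10% | 59% | 56% |
| Retention of 80% | 53% | 49% |
| True telehealth effect 105% of traditional | 51% | 48% |
| True telehealth effect 110% of traditional | 70% | 66% |
| True telehealth effect 115% of traditional | 85% | 81% |

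**What would give 80% power, changing one input at a time** (first figure 44/44/22, second 40/40/20)

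- Retention fraction: about 72.5%, or 71%.
- SD: 2.67, or 2.55.
- True traditional-versus-control effect: about 18.7, or 19.6 points.
- True telehealth effect: about 13.5%, or 14.5%, better than traditional.

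**Sample size for 80% power on the stated inputs**

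n per training arm = 25 × (1 + 0.7225 + 2 × 0.0225) × (1.960 + 0.842)² / 1.5² = 44.19 × 7.849 / 2.25 ≈ 154. With 77 controls the total is about 386 evaluable (2.5 × 154.14 = 385.4), and 385.4/0.90 ≈ 428 randomized, against 110.

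**An illustration**

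Suppose the two training arms have equal observed means, the observed traditional-versus-control difference is the planned 10 points, and the SD is as planned. The lower bound is then 1.5 − 1.96 × 1.002 = −0.46, and the criterion fails. With equal training-arm means it is met only once the observed difference exceeds 1.96 × 1.002/0.15 = 13.1 points.

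**The case against.** The strongest reply is that the non-inferiority sentence lists no inputs of its own. The 10% and 5% are attached to the superiority comparison, the true telehealth effect is nowhere stated, and the article is a condensed account whose software inputs are not shown. On that view one can say only that the figure cannot be reproduced, and the misreported number might be the retention fraction or the SD rather than the power. It is true that the cause cannot be identified from the article. But the article offers a single set of inputs for a single three-arm calculation, and on that set the stated power is wrong. Equality is also the natural alternative: the rationale section asks whether telehealth gives equivalent results and regards supervised facility training as probably the best setting.

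A second reply is that the analysis adjusts for the stratification factors, including baseline capacity, which could reduce the residual SD. If the 5% is an unadjusted SD (not stated), removing 30% to 50% of the variance would give 43% to 56% power at 44/44/22 and 40% to 52% at 40/40/20. Reaching 80% would mean removing about 71% of the variance, or about 74% after dropout. The article claims no such gain.

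Finally, no passage says that a failed test would be read as inferiority. That is a risk of interpretation, not something the plan states.

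**Conclusion.** The concern holds. On the stated sample size, effect, SD, retention fraction and α, the non-inferiority test has about 32% power, or about 30% at the expected number of completers, not 80%. The shortfall is about 50 percentage points, too large for rounding or choice of method to explain. The result assumes that telehealth is truly equal to traditional training and that covariate adjustment does not reduce the 5% SD. Relaxing either assumption within a plausible range raises the power but does not restore 80%. Under these assumptions an equally effective telehealth programme would fail the test about seven times in ten. Because the test serves a primary objective, the statement must be corrected.

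**What to change.** 1. Recover the original software inputs and reconcile them with the published ones. If the inputs stand as printed, correct the power statement: with 44/44/22 the 85% retention test has about 30% power allowing for dropout. At the same 10% and 5%, 80% power applies only to a retention fraction of about 71% to 72.5%. State the assumed true telehealth effect.
2. Before outcomes by arm are seen, choose one course. Either keep 85% and report its real power, or pre-specify another retention fraction. A new fraction needs a justification based on how much loss of effect is acceptable; that the sample size can support it is not enough.
3. Name the tested contrast, T − 0.85R − 0.15C, with non-inferiority concluded if its one-sided 97.5% lower bound exceeds zero.
4. In either case report the estimated retained fraction with its confidence interval, and state that failing to show non-inferiority will not be read as inferiority.

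The cost is protocol and SAP wording, and a much less favourable power figure on record. No further participants are required. Keeping both 85% retention and 80% power would instead take about 428 randomized.

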##### Children

A total of 70 children with a Fontan circulation (35 in the training group and 35 in the usual care group) is required to achieve >99% power (two-sided α of 5%) to detect a difference in peak VO_2_ of 10 ± 5% at 4-months.

#### Statistical Analysis

The primary analysis will be based on intention-to-treat (ITT), including all randomized participants regardless of exposure to the allocated treatment or adherence to the trial protocol. Comparison of the primary outcome measure (change in peak VO_2_ at 4-months) between the groups will be estimated using linear regression adjusted for the stratification factors used during randomization. Results will be presented as the difference of means with a corresponding 95% confidence interval (CI) and *p*-value. Secondary outcomes at 4-months and 12-months will be compared between the groups using linear regression with adjustment for the stratification factors for continuous outcomes and binary regression adjusted for the stratification factors used during randomization for binary outcomes where results will be presented as a risk difference and corresponding 95% CI.

For each participant cohort, if the proportion of missing data for the primary outcome is more than 5%, analysis based on multiple imputation may be performed. A sensitivity analysis to compare the results of analyses restricted to participants with complete data and analyses where those with missing data are included using multiple imputation will be performed. If used, multiple imputation models will be conducted for the outcome variable, and 50 completed data sets will be imputed by chained equations, including all the participants initially randomized. The primary outcome, randomization strata variables and variables predictive of (i) missingness and/or (ii) the change in peak VO_2_ will be included in the imputation model.

### Exercise Training and Physical Activity Interventions

#### Exercise Training Interventions for Adolescents and Adults

##### Traditional Fitness Facility-Based Exercise Training

Patients randomized to the traditional model of exercise training delivery will participate in moderate-to-vigorous intensity aerobic and resistance exercise training three times a week for 4-months. All sessions will be supervised by a qualified exercise professional (e.g., exercise physiologists or and physiotherapists) in small groups of 1-4 people. The sessions will be supervised in a local fitness facility near the participant's residence, where they will be provided with a complimentary membership for the duration of the study. Participants will start and conclude each session with a 5 min warm-up and cool down, which may include low-intensity exercise and dynamic or static stretching. The structure of the sessions will involve 10 min of aerobic exercise, 30 min of resistance exercises, followed by another 10 min of aerobic exercise.

The first 10-min bout of aerobic exercise will be performed on a cycle ergometer, and the second 10-min bout is selected based on the participant's preference to allow for autonomy. Aerobic exercise training will start at a moderate intensity (40-50% HRR) and progress up to vigorous intensity (70-80% HRR) after 10 weeks, as tolerated. The aerobic exercise training work rate will be continually adjusted throughout the program to maintain the target training HR range.

Resistance training will comprise of 5 exercises, including the leg press, seated row, leg curl, chest press, and calf raise. The participant's one-repetition maximum (1RM) will be assessed for each exercise during the first session and every 4 weeks to titrate the load to the appropriate training intensity. Resistance exercise intensity will start at 3 sets of 8-12 repetitions at 60% 1RM and be progressed to 70% 1RM after 2 weeks. Participants will be provided with ~60 s rest between sets. Consistent with clinical practice, intensity can be up titrated based on the participant's rating of perceived exertion (RPE) and observer RPE for aerobic exercise training using the OMNI scale. For resistance exercises, the two for two method, and the participant's or observer's RPE using the OMNI scale can be used to facilitate progression in between 1RM tests, which can be guided by the supervising exercise professional. An outline of the method of progression is shown in Table 3. The total estimated duration of each session is 60-75 min.

**Table 3 T3:** Exercise training progression for the traditional group.

**Weeks (sessions)**	**Intensity category**	**Intensity**
**Aerobic exercise training progression**		
1-2 (6)	Moderate	40-50% HRR
3-6 (12)	Moderate	50-60% HRR
7-10 (12)	Vigorous	60-70% HRR
11-16 (18)	Vigorous	70-80% HRR
**Resistance exercise training progression**		
1-2 (6)	Moderate (moderate load)	60% 1RM (3 sets, 8-12 repetitions)
3-16 (42)	Vigorous (moderate-to-high load)	70% 1RM (3 sets, 8-12 repetitions)

*HRR, Heart rate reserve; 1RM, one-repetition maximum*.

##### Telehealth Exercise Training

People in the telehealth group will participate in partially supervised moderate-to-vigorous intensity aerobic and resistance exercise training 3 times a week for 4-months. Prior to each session, a 5-min warm-up and cool-down will be performed and may include low-intensity exercise and dynamic or static stretching. Participants will be provided with a Gymstick™ and HR monitor for exercise training. Participants will be asked to perform 20 min of aerobic exercise training independently three times a week, starting at 40-50% HRR and progressing to 70-80% HRR. The aerobic exercise training progression will be consistent with the traditional group shown in Table 3. Exercise training HR will be transmitted to a mobile app, and participants will be asked to record the average and maximal HR as well as their RPE and session duration of each aerobic session in a training log.

Resistance exercise sessions will be supervised by qualified exercise professionals and delivered via Zoom in groups. Participants will perform 3 sets of 8-12 repetitions of various resistance exercises using a Gymstick™ with a target RPE of 7 using the OMNI scale by week 3 for each exercise. Resistance exercises may include squats, upright rows, lunges, seated rows, chest press, and calf raises. When the participant rates an exercise lower than 7 on the OMNI scale in consecutive sets or sessions, the resistance (load) of the Gymstick™ will be increased or participants will be asked to increase their repetitions to the upper limit of the prescribed range. Similar to the traditional group, the intensity can be adjusted based on the two-for-two method and observer RPE. Participants will also be asked to record exercise session details in a training log. The total estimated time to complete both the aerobic and resistance exercise session is ~60-75 min.

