### Randomization and Stratification

The F-FIT will involve three arms in adolescents and adults (≥16 years), and two arms in children (<16 years). Adolescents and adults will be randomized in an allocation of 2:2:1 to either a traditional gym-based exercise program (traditional group), a telehealth exercise training program (telehealth group), or usual care (control group), respectively. Children will be randomized to either an exercise training program or usual care (control group) based on a 1:1 allocation. Randomization will be stratified by: baseline aerobic exercise capacity (<65% or ≥65% predicted peak VO_2_); sex (male or female); and age (16-34 years or 35-55 years for adolescents and adults; 10-12 years or 13-15 years for children). Computer-generated, random permuted blocks will be prepared by an independent statistician in the Clinical Epidemiology and Biostatistics Unit (CEBU) at Murdoch Children's Research Institute (MCRI) and incorporated into the REDCap randomization tool (hosted by MCRI) that will be embedded in the REDCap database created for this trial. The randomization schedules will be prepared for each recruitment site.

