#### Children's Physical Activity Program

Children allocated to the intervention group will participate in a face-to-face physical activity program once a week for 4-months. The SAAFE principles will be utilized to guide the delivery of the program in an engaging and enjoyable manner (131). Weekly sessions will be supervised by an exercise professional and conducted at a community sport center or fitness facility near the participant's residence in small groups of 3-10 participants/family members when possible. The duration of each session will be ~90 min and consist of an exercise training circuit, foundational movement skills practice, and physically active games. Prior to each session, participants will engage in a 5-10 min warm-up that includes a variety of games, aerobic exercises, and dynamic stretching.

Participants will be provided with HR monitors that will transmit their HR in real-time to an app on an electronic device (e.g., iPad, tablet, or laptop) to monitor exercise intensity during the exercise circuit. The exercise circuit will be conducted in an interval format and encompasses a combination of aerobic and resistance exercises. Exercises may include but are not limited to squats, hopping, broad jumps, push-ups, backward running, and walking lunges. The target session average HR will initially be at moderate intensity (≥40% HRR) and progress to vigorous intensity (≥70% HRR) after 10 weeks, consistent with the adolescent and adult aerobic exercise programs (Table 3). The exercise circuit will last ~30 min.

Following the exercise circuit, participants will practice a variety of foundational movement skills (e.g., kicking, catching, throwing, and hitting) for 5-10 min, which is facilitated by the exercise professional, family members, and caregivers. After the practice period, participants will engage in physically active games for ~20 min. Each session will conclude with a 5–10 min cool-down that may consist of low-intensity aerobic activities and stretching.

In addition to the weekly face-to-face physical activity sessions, participants will also be provided with a variety of tasks to complete in their own time. These tasks will be directed at promoting a healthy lifestyle or complement the physical activity sessions.

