### Usual Care

Participants randomized into the usual care (control) group will continue with routine clinical care as directed by their treating medical team. They will also be instructed to continue with their usual daily activities and will not be restricted or asked to refrain from engaging in physical activity or exercise training. Participants allocated to the usual care group will be offered 4-months of telehealth exercise training (in adolescents and adults) or the physical activity intervention (in children) after their final 12-month testing session.

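### Supervised training is given in groups in the intervention arms only, but the stated regression treats participants as independent; if outcomes correlate within group or supervisor, error rates will exceed nominal, mainly for non-inferiority.

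*Protocol article*

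**What the plan says.** Participants are randomised individually, and supervised training is then delivered in groups in the intervention arms only.

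- Traditional arm (Traditional Fitness Facility-Based Exercise Training): every session is supervised, "in small groups of 1-4 people".
- Telehealth arm (Telehealth Exercise Training): "Resistance exercise sessions will be supervised by qualified exercise professionals and delivered via Zoom in groups". No group size is given. The aerobic part is done alone: "Participants will be asked to perform 20 min of aerobic exercise training independently three times a week".
- Children's intervention arm (Children's Physical Activity Program): weekly sessions "in small groups of 3-10 participants/family members when possible".
- Usual care (Usual Care): these participants "will continue with routine clinical care as directed by their treating medical team". They are offered training only after the 12-month assessment.

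Under Statistical Analysis, the change in peak VO2 at 4 months "will be estimated using linear regression adjusted for the stratification factors used during randomization". Those factors are given under Randomization and Stratification: "Randomization will be stratified by: baseline aerobic exercise capacity (<65% or ≥65% predicted peak VO_2_); sex (male or female); and age". None of them identifies a training group or a supervisor. Continuous secondary outcomes at 4 and 12 months use the same model. The Power Analysis section allows for 10% dropout and mentions no ICC or design effect.

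**The concern.** This is a partially nested design: the intervention arms can have clusters and usual care has none. Ordinary regression assumes independent residuals. A shared supervisor or shared sessions can make outcomes within a group more alike. The protocol leaves room for this, because the supervising professional may guide progression between strength tests, and the observer's rating of exertion may be used to adjust intensity in both adult arms.

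Where such correlation exists, the variance of an intervention-arm mean is larger than the model reports, so intervals are too narrow and tests reject too often. This matters most for telehealth against traditional training. That comparison is a primary objective with a tight criterion (at least 85% of the effect retained), and both arms are delivered in groups. A standard error that is too small there makes a false claim of non-inferiority more likely.

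**Working it through.** **Inputs from the protocol.** Adults 44/44/22; children 35/35; difference 10, SD 5 (percent); retention 85%; one-sided 2.5% for non-inferiority and two-sided 5% for superiority.

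**Inputs assumed, because the protocol does not give them.** ICC 0.02, 0.05 and 0.10; telehealth groups of 4 to 10; 2 to 6 trial children per group; groups that act as stable clusters; a retention test that uses the ordinary regression standard error. Gym groups of 1 to 4 are as stated.

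**1. The plan's own figures, without clustering.**

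- Adult superiority: SE = 5 × √(1/44 + 1/22) = 1.306 and 10/1.306 = 7.66. Power is above 99.9%, consistent with the stated minimum of 80%.
- Children: SE = 5 × √(2/35) = 1.195 and 10/1.195 = 8.37. Power is above 99.9%, consistent with the text.
- Non-inferiority: retention of 85% means telehealth − 0.85 × traditional − 0.15 × control ≥ 0. The variance factor is 1/44 + 0.7225/44 + 0.0225/22 = 0.04017, so SE = 5 × √0.04017 = 1.002. If telehealth equals traditional, the contrast is 0.15 × 10 = 1.5 and power is Φ(1.5/1.002 − 1.960) = 32%, against the stated 80%. That gap has nothing to do with clustering and is a separate matter. The error rates below depend only on the ratio of true to reported variance, so it does not affect them.

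**2. Non-inferiority error with clustering.** Each grouped arm's variance is multiplied by 1 + (m − 1) × ICC, where m is its group size; control keeps 1. Then

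ratio = [(1 + (m_tele − 1) × ICC)/44 + 0.7225 × (1 + (m_gym − 1) × ICC)/44 + 0.0225/22] / 0.04017,

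and the true one-sided error = 1 − Φ(1.960/√ratio).

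Example with telehealth groups of 6, gym groups of 3 and ICC 0.05: 1.25/44 + 0.7225 × 1.10/44 + 0.0225/22 = 0.04749. The ratio is 1.182 and its root 1.087; 1.960/1.087 = 1.803; the error is 3.57%.

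| ICC | Telehealth 4, gym 1: ratio, error | Telehealth 6, gym 3: ratio, error | Telehealth 10, gym 4: ratio, error |
|---|---|---|---|
| 0 | 1.000, 2.50% | 1.000, 2.50% | 1.000, 2.50% |
| 0.02 | 1.034, 2.70% | 1.073, 2.92% | 1.126, 3.24% |
| 0.05 | 1.085, 2.99% | 1.182, 3.57% | 1.316, 4.38% |
| 0.10 | 1.170, 3.50% | 1.365, 4.67% | 1.632, 6.25% |

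Simulation (40,000 runs, pooled-variance t test) agrees closely: 3.0% for groups of 4 and 1 at ICC 0.05; 3.9% for groups of 8 and 4 at ICC 0.05 (formula 4.0%); 5.4% for the same groups at ICC 0.10 (formula 5.6%).

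**3. Children.** Ratio = [(1 + (m − 1) × ICC) + 1]/2; two-sided error = 2 × [1 − Φ(1.960/√ratio)].

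| ICC | 2 trial children per group: ratio, error | 6 trial children per group: ratio, error |
|---|---|---|
| 0.02 | 1.010, 5.1% | 1.050, 5.6% |
| 0.05 | 1.025, 5.3% | 1.125, 6.5% |
| 0.10 | 1.050, 5.6% | 1.250, 8.0% |

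**4. Superiority at the planned effect.** Adults, worst case shown (gym groups of 4, ICC 0.10): the ratio is (1.3/44 + 1/22)/(1/44 + 1/22) = 1.10, so the two-sided error is 6.2%. The true SE is 1.369 and 10/1.369 = 7.30, so power stays above 99.9%. Children, 6 per group at ICC 0.10: SE = 5 × √(2.5/35) = 1.336 and 10/1.336 = 7.48, so power is again above 99.9%.

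**The case against.** The strongest reply is that nothing in the protocol establishes correlation within groups. No ICC, telehealth group size or statement that groups and supervisors stay fixed is given. Training is prescribed individually: heart-rate targets come from the participant's own exercise test, gym loads from the participant's own strength test, and telehealth loads from the participant's own rating. Telehealth aerobic work is done alone, and the primary outcome is aerobic capacity. A gym group may be one person at a facility near home. The children's group size counts family members and applies only when possible. All of this stands, and it points to weak clustering.

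A reader might infer that the standard errors are certainly too small and the 2.5% level is certainly breached. The documents do not support that: at ICC 0 the level is exact. A reader might also infer that participants share one group and supervisor for up to 48 sessions. Table 3 does give 48 sessions for the traditional arm, but constancy of groups is never stated, and the children's face-to-face programme is weekly, about 16 sessions over 16 weeks.

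It can also be said that an article leaves variance estimation to the full protocol or analysis plan, neither of which is shown. That is partly right. Those documents may already handle clustering, and the article does not say how the variance of the retention test is computed. But the article names a specific primary model, and that model has no term for group or supervisor.

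Finally, with telehealth groups of 6 there would be about seven groups (44/6), and about six for children (35/6). A group variance would be poorly estimated, which argues against insisting on one mixed model as primary.

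**Conclusion.** The point holds conditionally. The stated model does not match the stated delivery, and any positive correlation within group or supervisor would make its standard errors too small. Under the assumptions above, the true standard error of the retention contrast is about 1.02 to 1.28 times the reported one for ICC 0.02 to 0.10. The one-sided error is then modestly above 2.5% at low ICC and reaches about 6.2% only with the largest groups and the highest ICC considered. The children's two-sided error ranges from 5.1% to 8.0%, with the upper end requiring six randomised children per group. Neither superiority conclusion is at risk at the planned effect. The non-inferiority claim is the main exposure. The effect on secondary outcomes was not quantified. This is a worthwhile, inexpensive correction, not a flaw that invalidates the trial.

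**What to change.** Record a training-group identifier and a supervising-professional identifier for each participant during delivery, with any changes, since these may be hard to reconstruct later.

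Pre-specify an analysis that allows for clustering in the intervention arms only. Either of these would serve:

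- a partially nested mixed model, with usual-care participants as singletons and small-sample degrees of freedom (Satterthwaite or Kenward-Roger); or
- the planned regression with a cluster-robust variance corrected for few clusters.

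If ordinary regression stays primary, make this a sensitivity analysis that the non-inferiority claim must withstand. Report the estimated ICC with its interval. If the full protocol or analysis plan already provides for this, the article's model statement should be aligned with it.

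The cost is one or two data fields, slightly wider intervals, and a group variance that will be imprecise because there are few groups.
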